### Randomization and Blinding

Randomization will be performed by a computer-generated randomization schedule that will assign participants 1:1 to either MW189 or placebo. The allocation sequence will be created and stored in a protected electronic data capture system. All providers and nurses participating in the treatment plan will be excluded from data and outcome analyses. The observers who assess the clinical outcomes will be blinded to the randomization results. A safety review will be performed in a blinded manner unless the data warrants unblinding because of the nature of any safety concerns. When unblinding is required, requests will be directly forwarded to the study’s unblinded statistician by the site investigator. To further maintain blinding during study drug administration, the IV equipment will be covered. Once the study drug is diluted, it must be stored at ambient temperature and protected from light until administration.

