### Sample Size Determination

The primary outcome of the study is to measure the proportion of participant deaths from any cause within the first 7 days after randomization. We anticipate that the mitigation of inflammation and edema will lead to fewer deaths in the MW189 arm during the acute phase. However, with an abundance of caution, we assume the placebo arm will have a similar number of deaths as compared to the MW189 arm. Therefore, we conducted a noninferiority power analysis using previously collected data from the Minimally Invasive Surgery Plus Alteplase for Intracerebral Hemorrhage Evacuation (MISTIE) III [27] and Antihypertensive Treatment of Acute Cerebral Hemorrhage II (ATACH-2) trials [28] to approximate the safety events that will be seen in the trial.

Considering a power of 80% and a one-sided 90% confidence interval, to test the null hypothesis of noninferiority with a tolerance limit of 12% and assuming a “worst-case” safety assumption of 10% rate of death in each arm, the sample size per group was estimated to be 57. We assume a low overall withdrawal rate in the first 7 days, and therefore 120 participants (60 per group) are required to evaluate the safety of MW189. This number also meets the estimated sample size for an 80% power and two-sided *α* to detect various assumed differences in PHE volume and maximum observed effect (*E*_max_) values in the interleukin-10 plasma cytokine response between treatment arms.

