### Statistical Analyses

The intention-to-treat analysis set (all randomized participants) will be used for efficacy analysis. All participants who receive any study treatment will be included in the safety analyses. Continuous variables of normal distribution will be expressed as mean ± standard deviation, whereas continuous variables of nonnormal distribution will be expressed as median and interquartile range. Categorical variables will be represented as frequencies and percentages. We anticipate no missing data for the primary outcome, as all-cause mortality within 7 days of treatment initiation is verifiable.

The primary outcome will involve an estimate of the difference in the proportion of all-cause mortality within 7 days of treatment initiation using a 90% one-sided confidence interval on the upper bound of this difference. The null hypothesis will be rejected if this confidence interval is less than 10%. In addition, we will also estimate the treatment difference in the proportion of 7-day all-cause mortality using a multivariable logistic regression model. This model will consider age, sex, race and ethnicity, ICH volume at stability, Glasgow Coma Scale (GCS) score, presence of IVH, withdrawal of life-sustaining therapy, and ICH location (deep versus lobar). This trial encompasses infratentorial ICH, which comprises brainstem ICH classified as deep location and cerebellar ICH classified as lobar location. Age, sex, and race and ethnicity data are collected at the screening visit. The GCS score is measured at baseline. Presence of IVH and ICH location are determined based on the diagnostic CT scan. The ICH volume assessed on the stability CT scan determines the need for additional imaging to establish hematoma at 6-h intervals until the end of the enrollment period. Withdrawal of life-sustaining therapy information is collected at any time during the study period. The schedule of activities is detailed in Table 2.

**Table 2 Tab2:** Schedule of activities

Activities	Screening/enrollment first dose	Treatment				Follow-up		
Day	1	2	3	4	5	30 (clinic)	90 (phone)	180 (clinic)
Time frame	First dose within 24 h of ICH onset							
Pre-randomization								
Diagnostic CT	X							
CTA/MRI to rule out underlying lesion	X							
Inclusion/exclusion criteria review	X							
Consent by participant or legally authorized representative	X							
MRI to rule out underlying lesion	X							
Stability CT	X							
Pregnancy test	X							
Demographics	X							

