Medical history and admission information	X							
Concomitant medications review	X							
At randomization								
Vital signs	X							
Glasgow Coma Scale	X							
Baseline (premorbid) modified Rankin Scale (caregiver interview)	X							
Post randomization								
Research MRI					X			
Usual care clinical CT		X	X	X				
Research CT					X			
Therapy intensity level	X	X	X	X	X			
National Institutes of Health Stroke Scale	X	X	X	X	X	X		X
Glasgow Outcome Scale-Extended						X	X	X
Glasgow Coma Scale	X	X	X	X	X	X		X
Montreal Cognitive Assessment					X	X		X
Stroke Impact Scale-16					X	X		X
Barthel Index	X				X	X	X	X
Modified Rankin Scale						X	X	X
EQ-5D						X	X	X
Center for Epidemiological Studies–Depression						X	X	X
Concomitant medications review		X	X	X	X	X	X	X
Plasma biomarkers	X		X		X			
Cerebrospinal fluid biomarkers	X		X		X			
Pharmacokinetic blood samples	X	X	X		X			
Dosing	X	X	X	X	X			
Adverse events assessment	X	X	X	X	X	SAE/MEOI	SAE	SAE

CT, computed tomography; CTA, computed tomography angiography; ICH, intracerebral hemorrhage; MEOI, medical event of interest; MRI, magnetic resonance imaging; SAE, serious adverse events

Secondary and exploratory safety outcomes will be analyzed using appropriate linear or logistic regression models and will account for treatment group, age, GCS score, presence of IVH, ICH volumes, the timing of drug administration, and hematoma location. No imputation of missing safety end points will be used. Instead, sensitivity analyses will be performed, whereby participants with missing secondary safety data will be assumed to have had a safety event and then not to have had a safety event. The analyses will account for the variability in dosing and treatment duration, which can range from 2 to 10 doses depending on the date of discharge. This variability will be addressed through various approaches, such as categorizing participants into dose groups, treating the number of doses as a continuous variable, and calculating area under the curve that considers the dose and duration of the doses given. The point estimate of the proportion of total safety events and corresponding two-sided 95% confidence intervals will be calculated under both extreme scenarios to provide estimates of uncertainty in the presence of these missing data. SAS, STATA 17, and/or R software will be used for statistical analysis. Statistical significance will be set at *p* < 0.05.

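### The two stated scenarios for missing secondary safety data bound the event proportion but not the MW189–placebo difference

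*Protocol article*

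**What the plan says.** All of this is in the Statistical Analyses section of the protocol article.

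- Main analysis: "Secondary and exploratory safety outcomes will be analyzed using appropriate linear or logistic regression models and will account for treatment group", along with several baseline covariates. For these outcomes the planned estimate is therefore a between-arm comparison.
- Missing values in that analysis: "No imputation of missing safety end points will be used".
- Sensitivity analysis: "participants with missing secondary safety data will be assumed to have had a safety event and then not to have had a safety event". No assignment by arm is described.
- Output: "The point estimate of the proportion of total safety events and corresponding two-sided 95% confidence intervals will be calculated under both extreme scenarios", with the purpose "to provide estimates of uncertainty in the presence of these missing data". The text does not say whether the proportion is pooled or given by arm, and it names no treatment difference.
- Primary outcome: "We anticipate no missing data for the primary outcome".

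The trial randomizes 1:1, and the Sample Size Determination section states that "120 participants (60 per group) are required to evaluate the safety of MW189".

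**The concern.** The main analysis compares arms, but the stated sensitivity analysis moves both arms in the same direction. When the missing counts are similar, the shift cancels in the difference, however much is missing. The case that matters most for a safety comparison is that missing MW189 participants had events and missing placebo participants did not. It lies outside the two stated scenarios.

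Some missingness is plausible for these outcomes. Follow-up in Table 2 runs to day 180, whereas the assumption of low withdrawal in Sample Size Determination covers only the first 7 days. Treatment can end early at discharge, and the research CT is scheduled on day 5, so a participant discharged before then may lack the scan that informs hematoma expansion.

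At stake is how the results are read. Under balanced missingness, a statement that the treatment comparison is robust to missing data would rest on an analysis that could not have shown otherwise.

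**Working it through.** **The plan's own figure.** The article gives no figure for the missing-data scenarios. Its one reproducible figure, 57 per group, comes from the primary noninferiority calculation. With 10% mortality per arm, a 12-point margin, one-sided 10% significance and 80% power, n = 0.18 × (z₀.₉₀ + z₀.₈₀)² / 0.12² = 56.35, which rounds up to 57. The figure reproduces. The present point does not depend on it.

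**Inputs**
- From the article: n = 60 per arm, and the two scenarios.
- Assumed: 6 observed events per arm (10%), and 1 to 9 missing per arm (1.7% to 15%). The article gives neither for secondary safety outcomes.

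**Algebra.** Let e₁ and e₀ be observed events, m₁ and m₀ missing counts (1 = MW189, 0 = placebo), and d = (e₁ − e₀)/n.
- All missing = no event: difference = d.
- All missing = event: difference = d + (m₁ − m₀)/n.
- MW189 missing = event, placebo missing = no event: d + m₁/n, the upper bound.
- The reverse: d − m₀/n, the lower bound.

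The planned pair spans |m₁ − m₀|/n, and the attainable range spans (m₁ + m₀)/n. The two are equal only if m₁ or m₀ is zero.

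**Numbers.** Differences are in percentage points, MW189 minus placebo, with Wald 95% CIs: d ± 1.96 × √[p₁(1 − p₁)/60 + p₀(1 − p₀)/60].

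| Missing (MW189, placebo) | All no event | All event | Crossed, worst for MW189 | Crossed, best for MW189 |
|---|---|---|---|---|
| 1, 1 | 0.0 (−10.7 to 10.7) | 0.0 (−11.5 to 11.5) | +1.7 (−9.5 to 12.8) | −1.7 (−12.8 to 9.5) |
| 3, 3 | 0.0 (−10.7 to 10.7) | 0.0 (−12.8 to 12.8) | +5.0 (−6.8 to 16.8) | −5.0 (−16.8 to 6.8) |
| 6, 6 | 0.0 (−10.7 to 10.7) | 0.0 (−14.3 to 14.3) | +10.0 (−2.7 to 22.7) | −10.0 (−22.7 to 2.7) |
| 9, 9 | 0.0 (−10.7 to 10.7) | 0.0 (−15.5 to 15.5) | +15.0 (1.7 to 28.3) | −15.0 (−28.3 to −1.7) |
| 6, 3 | 0.0 (−10.7 to 10.7) | +5.0 (−8.6 to 18.6) | +10.0 (−2.7 to 22.7) | −5.0 (−16.8 to 6.8) |
| 6, 0 | 0.0 (−10.7 to 10.7) | +10.0 (−2.7 to 22.7) | +10.0 (−2.7 to 22.7) | 0.0 (−10.7 to 10.7) |

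Worked case for 6 missing per arm, worst for MW189: 12/60 − 6/60 = 0.10. The standard error is √(0.16/60 + 0.09/60) = 0.0645, and 1.96 × 0.0645 = 0.127, giving −2.7 to 22.7 points.

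With 12 observed events per arm the point differences are unchanged and the intervals are wider; the same crossed case becomes +10.0 (−5.4 to 25.4).

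**The proportion itself.** With 6 missing per arm the planned scenarios give 6/60 = 10% and 12/60 = 20% in each arm, and 12/120 = 10% and 24/120 = 20% pooled. Those bounds are correct.

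**The case against.** The strongest reply is that the plan does what it says. The output it names is a proportion of safety events, and for a proportion the all-event and no-event assumptions are the correct and complete bounds. That stands. A reader might infer that the plan understates the very uncertainty it sets out to quantify. The text does not support this, because it never claims to bound the treatment difference.

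A reader might also infer that no arm-specific scenario is planned anywhere. That cannot be established either: this is a condensed article, and the full protocol and SAP are not shown. The point is confined to the method the article states, which does not test the comparison planned for the same outcomes.

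Three further replies stand in part.

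- Unequal missingness is partly picked up. With 6 missing against 3, the all-event scenario moves to +5.0, and with 6 against 0 it reaches the full bound of +10.0. The gap is widest when the counts are equal but the reasons differ by arm.
- If proportions are reported by arm, a reader could cross them by hand for the crude difference. The article does not say that they will be, and this would not give the adjusted regression estimate.
- The practical stakes are limited. The primary outcome is expected to be complete, much of the adverse-event recording takes place in hospital, and no missingness rate is given. With 1 missing per arm the effect is 1.7 points. The article states no margin or decision rule for secondary safety outcomes, so no stated decision turns on the result.

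**Conclusion.** The point holds as an inexpensive improvement to a stated method. The two scenarios bound event proportions. They do not bound the MW189–placebo difference unless all missing data fall in one arm; that follows from the algebra and needs no assumed rate.

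The size does rest on assumptions. At 60 per arm, the part of the attainable range left unexplored runs from ±1.7 points with 1 missing per arm to ±10.0 with 6 and ±15.0 with 9. If follow-up is nearly complete, the matter is small.

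The conclusion covers event-type secondary and exploratory safety outcomes only. It casts no doubt on the 7-day mortality analysis. A reader might go on to infer that a safety conclusion should count as robust only if it survives the worst crossed case. The article gives no margin for these outcomes against which survival could be judged, and that assignment is deliberately pessimistic, so the inference is not supported.

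**What to change.** Keep the two planned scenarios for the proportions. Add two crossed scenarios: missing on MW189 counted as an event with missing on placebo counted as no event, and the reverse. Under all four, report the treatment difference with its 95% CI, and give the number missing in each arm beside them. Describe the crossed scenarios as extreme bounds, not as a pass/fail rule.

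The change should be specified before unblinding. It costs two more runs on the same data and about one sentence of text, with no new data collection. The small downside is that the crossed intervals will be wide and deliberately pessimistic, and should be labelled so. A tipping-point analysis by arm would serve the same purpose.

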## Discussion

The primary objective of the BEACH trial is to assess if five consecutive days of MW189 treatment after spontaneous ICH is safe and does not increase early mortality. Prior nonclinical studies demonstrated that this novel investigational small-molecule drug candidate reduces a set of central nervous system inflammatory responses after brain injury by suppressing the production of excessive glial proinflammatory mediators. In an ICH mouse model, 5-day treatment with low doses of MW189 (1 mg/kg) significantly decreased cerebral edema post injury and reduced vestibulomotor deficits [17]. In preclinical safety, pharmacology, and toxicology studies, an IV formulation of MW189 was developed based on the standard route of administration in acute brain injury trials. Phase 1 clinical studies performed with this IV drug product demonstrated good tolerance and no treatment-related or treatment-emergent AEs, especially in vital organ systems. Importantly, when considering the anticipated pharmacologic effect of MW189, no alterations were observed in standard immunological parameters, including organ weights, hematology/blood cell counts, or microscopic and macroscopic evaluation of lymphoid and related tissues.

We added several points to the justification of the primary end point, time window, duration of treatment, and volume range of qualifying ICH. The selection of all-cause 7-day mortality as the primary outcome, the time window and duration of treatment with MW189, and the volume range of qualifying ICH (10–60 mL) are carefully justified based on clinical relevance and considerations and available preclinical and clinical evidence. First, the choice of all-cause 7-day mortality as the primary outcome in this trial is justified by its clinical significance and relevance in assessing the immediate impact of the intervention on early mortality rates. This end point provides valuable insights into the potential benefits of MW189 as a therapeutic intervention during the critical initial phase of acute spontaneous ICH. Second, regarding the time window and duration of treatment, preclinical studies and initial clinical data provided evidence of the drug’s therapeutic effects within a specific treatment duration [6, 13, 14]. By administering MW189 within 24 h of symptom onset and continuing treatment every 12 h for up to 5 days or until hospital discharge, we aim to maximize the drug’s potential neuroinflammation-reducing and cerebral-edema-attenuating effects. Lastly, the volume range of qualifying ICH between 10 and 60 mL was chosen because it reflects a clinically relevant and diverse range that encompasses a substantial proportion of spontaneous ICH cases. This allows for a comprehensive evaluation of MW189’s efficacy and safety across a diverse patient population with varying degrees of ICH severity, ensuring the generalizability of study findings.

Enrollment began in October 2022, and the estimated recruitment completion date is December 2025. Nine participants have been enrolled for the study as of August 2023. Recruitment will continue until the total sample size is achieved. There are no planned interim analyses.

MW189 holds promise for treating neuroinflammation in acute spontaneous ICH. BEACH, the first-in-patient, multicenter, placebo-controlled phase 2a trial assessing safety of MW189 in participants with ICH, will provide critical information about designing a larger phase 2b/3 trial to investigate efficacy of MW189. In addition, our secondary and exploratory analyses may identify mechanisms and biological responses to this new potential therapy targeted toward neuroinflammation and cellular brain injury.
